## Abstract

**Introduction:**

Chlorophyllin (CHL) effectively decreases the side effects of radiotherapy (RT) by scavenging radiation‐induced free radicals and reactive oxygen species in preclinical trials. This study aims to assess the efficacy of oral CHL for the treatment of brain radionecrosis in patients with diffuse glioma.

**Methods:**

This is a phase 2 trial prospective, interventional study. Adults (> 18 years) with a histological diagnosis of diffuse glioma developing radionecrosis will be eligible for the study. Radionecrosis will be identified using standard imaging protocols with magnetic resonance imaging (MRI) with or without positron emission tomography (PET). Patients will be accrued in two strata: symptomatic (stratum A) and asymptomatic (stratum B). Chlorophyllin will be prescribed to all patients using a morning oral dose of 750 mg before breakfast for 3 months. In addition, participants in stratum A will be given a tapering dose of dexamethasone for 1 month, while stratum B will not be receiving any steroids. Imaging with an MRI brain protocol and PET scan will be planned at 1 month and MRI at 3 months after starting CHL. The primary endpoint is the clinical‐radiological response at 1 month. Secondary endpoints include response at 3 months, biological responses, survival analysis, and quality‐of‐life scores. The total sample size is 118 (60 and 58 in stratum A and B, respectively), with one interim analysis planned.

**Discussion:**

Radionecrosis leads to significant morbidity and is usually treated with corticosteroids, which can lead to several side effects from both acute and long‐term use. Refractory radionecrosis requires treatment with bevacizumab or surgical resection. Chlorophyllin is a cheap, safe, and readily available phytopharmaceutical drug, which is being investigated in the phase 2 study and, if proven effective, can be considered an alternative for treating radionecrosis.

**Trial Registration:** Clinical Trial Registry India (CTRI): CTRI/2023/08/056166; ClinicalTrials.gov: NCT06016452

AbbreviationsCHLchlorophyllinCTcomputed tomographyCTCAEcommon terminology criteria for adverse eventsCTRTchemotherapy radiotherapyEORTCEuropean Organization for Research and Treatment of CancerGCPgood clinical practiceICDinformed consent documentICFinformed consent formKPSKarnofsky performance scaleMRImagnetic resonance imagingNANOneurologic assessment in neuro‐oncologyNPSneurological performance scalePETpositron emission tomographyPFSprogression free survivalQOLquality of lifeQTWiSTquality‐adjusted time without toxicityRNradionecrosisRTradiotherapyWBIwhole brain irradiation

## Introduction

1

Radiotherapy (RT) plays an integral role in the multimodality management of adult‐type diffuse gliomas. Radiation is indicated in adult‐type low‐grade gliomas with high‐risk features or high‐grade gliomas following maximal safe resection [1, 2, 3]. Higher doses of RT can lead to symptomatic radio‐necrosis (RN) in approximately 5%–15% of patients, typically within the first 2 years of RT completion [4, 5, 6, 7]. The development of RN can lead to significant morbidity, with new‐onset or worsening of pre‐existing neurodeficits having substantial implications for quality of life (QOL), and in extreme situations, can lead to mortality. The pathogenesis of RN is multifactorial, with a complex interplay of vascular‐mediated damage and injury to glial cells primarily postulated through the activation of several inflammatory markers like tumor necrosis factor, interleukins, and vascular endothelial growth factor [6]. Corticosteroids, preferably dexamethasone, form the first line of management of RN, with variable response rates ranging from 25%–60%, impacted by several factors like the dose of RT and response evaluation methods (neurological/radiographic) [8, 9]. The response rate in our practice concurs with the reported literature, with combined clinical and radiological responses seen in approximately 50% of patients from institutional experience and audit. It is important to note that the long‐standing use of corticosteroids comes at the cost of complications like hyperglycemia, myopathy, and increased risk of infections precluding prolonged use. Also, a proportion of patients remain refractory to steroids or turn out to be dependent on steroids, where bevacizumab (anti‐angiogenic agent) can be used as second‐line therapy in appropriately selected patients [10, 11]. However, the major disadvantages of bevacizumab remain intravenous administration, requiring regular hospital visits, treatment costs, and concerns for related toxicities like hypertension and intracranial or extracranial hemorrhage. Other agents like hyperbaric oxygen therapy, pentoxifylline, and tocopherol have been suggested in refractory radionecrosis, with questionable benefits [6].

Sodium‐copper‐chlorophyllin is a phytopharmaceutical drug obtained from the green plant pigment chlorophyll. It is a semi‐synthetic mixture of sodium copper salts derived from chlorophyll. Chlorophyllin scavenges RT‐induced free radicals and reactive oxygen species. It has been used as a food colorant and over the counter in the USA, Japan, Australia, and China for many years for various health benefits, including the prevention of body odor in geriatric patients, enhanced wound healing, antibacterial action, etc. [12]. Studies have shown that CHL has immunostimulatory, anti‐inflammatory, and antiviral effects in addition to antioxidant and radioprotective properties [13]. It increases the expression of a transcription factor (protein) Nrf2, improving lymphocyte survival and enabling efficient detoxification after RT exposure [14, 15].

The current study is a phase 2 study to investigate the role of CHL as an anti‐inflammatory agent in treating brain radionecrosis, a long‐term toxicity of cranial radiotherapy.

## Study Methodology

2

### A. Study Design/Population

2.1

This is a prospective phase 2 open‐label study conducted in a single institute. Patients with a histopathological diagnosis of adult‐type diffuse glioma treated with conventionally fractionated high‐dose radiotherapy developing radionecrosis will be eligible for the current study. Radionecrosis will be diagnosed using standard institutional protocols based on magnetic resonance imaging (MRI) and/or positron emission tomography (PET) as decided clinically. MRI will include standard brain protocol per institutional practice, including T1w pre‐ and post‐contrast, T2w propeller, T2 FLAIR, GRE/susceptibility sequences, ADC, DWI, spectroscopy, and perfusion‐weighted imaging. All the images will be reviewed independently by a neuroradiologist and nuclear medicine physician (as appropriate) and discussed in the multidisciplinary tumor board (in cases of indeterminate findings) to reach a consensus of RN and exclude the possibility of disease progression. For evaluating disease progression, the updated Response Assessment in Neuro‐Oncology criteria (RANO 2.0) will be used [16]. A patient with typical radiological findings of radionecrosis is presented in Figure 1. Patients will be assessed for the eligibility criteria below prior to inclusion in the study.

**FIGURE 1 cam470657-fig-0001:**
[figure not shown]
Radiological findings for a patient with radionecrosis. (A, B) show the presence of an enhancing rim with a central necrotic core along the right periventricular region. (C) is the corresponding T2‐weighted image showing significant edema. (D) is the F‐DOPA PET showing low‐grade avidity of the lesion.

### Inclusion Criteria

2.2

The histological diagnosis should be of adult‐type diffuse glioma.Radionecrosis on imaging with new neurological symptoms or worsening of prior deficits (Stratum A) or without new symptoms (Stratum B).The patient should be ≥ 18–70 years old during study accrual.The Karnofsky Performance Scale (KPS) should be ≥ 50.

### Exclusion Criteria

2.3

No tissue diagnosis.Patients with KPS < 50.Disease progression cases must be excluded.Contraindications to corticosteroids.Altered mental status with deficits in understanding or an inability to consent to the study.Brainstem glioma diagnosis patients should be excludedIndeterminate for radionecrosis vs. disease progressionThe patient undergoing prior treatment with bevacizumab (either for disease progression or radionecrosis)

### Study Intervention

2.4

After meeting study eligibility, written consent forms will be obtained from all the patients. Patients with symptomatic RN (new‐onset neurodeficit or worsening of prior deficit concurrently with imaging evidence of RN) and asymptomatic RN (no deficits or stable neurological status during imaging development of RN) will be accrued in strata A and B, respectively. The clinical status will be documented using the Neurological Performance Status (NPS) scale [17] and the Neurologic Assessment in Neuro‐Oncology (NANO) scale [18]. Patients in strata A will be treated with a tapering schedule of dexamethasone as per institutional practice, starting with 8 mg TDS for 5 days, followed by 4 mg TDS for 5 days, 4 mg BD for 5 days, 2 mg BD for 5 days, 1 mg BD for 5 days, and 1 mg OD for 5 days (cumulative duration 1 month). Patients in strata B will not be prescribed any steroids. Chlorophyllin will be prescribed to all patients using a morning oral dose of 750 mg before breakfast for a planned duration of 3 months. Imaging with an MRI brain protocol and amino acid PET scan will be scheduled at 1 month (additional examinations per study protocol) and MRI at 3 months (standard of care imaging) after starting CHL therapy. Repeat clinical evaluations with KPS, NPS, NANO, and QOL assessments will be done for all the patients at 1 month and 3 months from starting CHL.

### Response Evaluation

2.5

The study endpoints have been summarized in Table 1. Response to CHL will be considered as the absence of all three criteria as follows:
Imaging progression of radionecrosis: Defined as an increase in T1‐contrast or T2w hyperintensity of the index lesion on the MRI brain, as assessed by a neuroradiologist. The PET scan at 1 month will be assessed by the nuclear medicine physician, and findings will be interpreted based on the avidity of the index lesion.Clinical deterioration will be considered as a ≥ 2‐point drop in the NPS at assessment points (1 and 3 months) from baseline NPS.Dexamethasone requirement: Any increase in the dexamethasone requirement during the predetermined tapering schedule will be considered refractory RN for stratum A. Any requirement of dexamethasone after CHL will be considered a failure of CHL in stratum B. Similarly, after the 1st month (when no dexamethasone use is planned in stratum A), the use of dexamethasone will be considered a failure of CHL for stratum A during the analysis of response at the 3rd month.

**TABLE 1 cam470657-tbl-0001:** Objectives and endpoints of CHROME study.

Study objective	To assess the efficacy of oral CHL in the treatment of radionecrosis in patients with diffuse glioma
Study endpoints	
Primary endpoint	Response rates (clinical‐radiological) at 1 month with the use of CHL
Secondary endpoint	Clinical‐radiological response rates at 3 months Biological response rates using functional imaging (PET and MRI) Survival analysis (Progression‐free survival and overall survival) EORTC QOL C‐30 and BN‐20 questionnaire at baseline, 1‐month, and at 3‐month follow‐ups NANO scale score QTWIST score
Exploratory endpoint	Temporal changes of inflammatory and tumor‐related biomarkers obtained from the serum

Therefore, for study analysis, combined evaluation (radiological, clinical, steroid requirement) will serve as a method of testing the efficacy of CHL, with progression in any single domain of the above three considered a failure, as mentioned above. Patients with unequivocal disease progression on imaging at 1 or 3 months will be excluded from RN response assessment (since the possibility of recurrence component is likely to contribute to neurological functioning and outcomes). Any discrepancies or equivocal findings will be discussed in a joint neuro‐oncology meeting (JNOM) for a consensus decision. No additional follow‐up visits will be required as per study protocol since patients with RN are called at 1 month for clinical evaluation and at 3 months for radiological and clinical evaluation. However, additional imaging will be undertaken with MRI and PET scan at 1 month after starting CHL. Imaging with MRI brain tumor protocol will be done at 3 months as the standard of care following institutional practice. The study workflow has been presented in Figure 2. A subgroup analysis of response to chlorophyllin will be done for patients with IDH‐mutant and IDH‐wild gliomas for both strata. As a part of the study (exploratory endpoint), 12–15 mL blood samples (EDTA and plain tubes) will be collected at baseline, 1 month, and 3 months. The blood will be analyzed for inflammatory indices from routine hemogram serum biochemistry, including albumin, CRP, and ferritin, along with additional exploratory markers like cytokines, chemokines (GM‐CSF, IFN‐gamma, TNF‐beta, interleukins, etc.), oxidative stress markers, proteomics, and metabolomics.

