### Stratum A

2.7

The response rate at 1 month with a combination of steroids and CHL in this study is expected to be 65% as compared to the standard 50% response with the use of dexamethasone alone (based on institutional experience and available literature) [7, 8, 9, 19]. For the study with a α of 0.1 and power of 80%, 50 patients will be needed to achieve the desired output. In the first stage, 22 patients will be needed for assessment and continue to stage 2 if > 10 responses are seen. Stage 2 of the study will be considered successful if > 29 responses are achieved using the pre‐specified response assessment criteria. Further considering an attrition rate of 10% from lack of follow‐up and another 10% for disease progression, an estimated 60 patients will be accrued in stratum A with the purpose of achieving 50 patients with endpoints available for analysis.

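### Only dexamethasone counts as rescue failure, so a patient given bevacizumab or resection for radionecrosis can be scored as a chlorophyllin responder, mainly at 3 months

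*Protocol article*

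**What the plan says.** Section 2.5 (Response Evaluation) opens the definition with "Response to CHL will be considered as the absence of all three criteria as follows". It then lists imaging progression of the index lesion, clinical deterioration, and dexamethasone requirement. The same section repeats the rule for the analysis, with "progression in any single domain of the above three considered a failure". The only treatment that counts is dexamethasone: in stratum A, any increase during the taper, and any use after month 1 for the 3-month analysis; in stratum B, any use at all. The clinical criterion is a fall of at least 2 points, judged as a "drop in the NPS at assessment points (1 and 3 months) from baseline NPS".

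Other treatments for radionecrosis appear elsewhere in the article. The abstract states: "Refractory radionecrosis requires treatment with bevacizumab or surgical resection". The Introduction describes patients who "remain refractory to steroids or turn out to be dependent on steroids, where bevacizumab" can be used as second-line therapy, and the Discussion (section 3) also gives bevacizumab a role in refractory cases. Section 2.3 excludes "prior treatment with bevacizumab (either for disease progression or radionecrosis"), which covers the period before entry only. The one exclusion from response assessment after entry is for unequivocal tumour progression.

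**The concern.** The rule is stated twice and both times as complete, so an analyst who follows it has no basis for scoring any other rescue as failure. Take a patient who worsens between visits, receives bevacizumab or has the lesion resected, needs no further dexamethasone, and has a stable or smaller lesion and a stable NPS at month 3. None of the three criteria is met, and the patient is a responder to CHL although another therapy produced the result.

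This is inconsistent with the plan's own logic, which treats first-line rescue as failure but leaves second-line rescue unscored. It also fits poorly with the comparators. Section 2.7 sets stratum A against the "standard 50% response with the use of dexamethasone alone". Section 2.8 describes the 30% for stratum B as patients who stay stable or regress with no further treatment of any kind, steroids included.

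At stake is the 3-month response rate, which the Discussion presents as the measure of longer-term response to CHL. This kind of misclassification can move it only upward.

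**Working it through.** **Who can be misclassified**

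| Situation | Scored under section 2.5 |
|---|---|
| Dexamethasone increased during the taper (A), or any dexamethasone (B) | Failure |
| Dexamethasone after month 1 (A) | Failure at month 3 |
| Bevacizumab or resection together with extra dexamethasone | Failure, through the dexamethasone |
| Bevacizumab or resection, no further dexamethasone, lesion not larger, NPS not down by 2 points | Responder |
| Unequivocal tumour progression | Excluded |

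The fourth row is the gap.

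*Month 1.* The gap is narrow. Bevacizumab follows steroids, steroid rescue already counts, and no scheduled visit precedes month 1 (no additional follow-up "visits will be required as per study protocol since patients with RN are called at 1 month for clinical evaluation").

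*Month 3.* Two readings are open, and the article does not choose between them. If a month-1 failure does not carry forward, a patient who failed at month 1 and was then rescued can become a month-3 responder. If it does carry forward, only patients first rescued between months 1 and 3 are affected.

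**Inputs** (Table 2 and sections 2.7 and 2.8)
- Stratum A: null rate 50%, alternative 65%; continue if more than 10 of 22 respond, success if more than 29 of 50.
- Stratum B: null rate 30%, alternative 45%; continue if more than 6 of 23 respond, success if more than 18 of 48.
- Rate of non-dexamethasone rescue: not given in the article, and none is assumed.

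**Reproducing the stated design.** With stage-1 size n1, stage-1 limit r1, total n and final limit r, the probability of success at response rate p is the sum over x > r1 of Bin(x; n1, p) × P(Bin(n − n1, p) > r − x).
- A: 0.0977 at 50% and 0.8022 at 65%.
- B: 0.0963 at 30% and 0.8027 at 45%.

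Both pairs match Table 2.

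**Shift in the 3-month rate from k misclassified patients (k/n)**

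| k | A (n = 50) | B (n = 48) |
|---|---|---|
| 1 | 2.0 points | 2.1 points |
| 2 | 4.0 points | 4.2 points |
| 3 | 6.0 points | 6.3 points |

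If every accrued patient were evaluable, one patient would move the rate by 1/60 = 1.7 points (A) or 1/58 = 1.7 points (B).

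**For scale: 95% sampling half-width, 1.96 × √(p(1 − p)/n), at the null rates**
- A: 1.96 × √(0.50 × 0.50/50) = 0.139, or 13.9 points.
- B: 1.96 × √(0.30 × 0.70/48) = 0.130, or 13.0 points.

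**Effect on the 1-month decision.** One misclassified stage-2 patient changes the final call only if stage 1 was passed and the true count is exactly 29 (A) or 18 (B). At the null rate p0, that probability is the sum over x > r1 of Bin(x; n1, p0) × Bin(r − x; n − n1, p0).
- A: 0.054.
- B: 0.057.

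Even then, an unscheduled early rescue that bypasses steroids would also be needed.

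**The case against.** The strongest reply is that the treatment pathway closes most of the gap. Dexamethasone is the institution's first-line treatment for symptomatic radionecrosis. A worsening stratum B patient would normally receive it first and so be a failure. A steroid-dependent stratum A patient is caught by the existing rule. What remains is mainly a stratum A patient who completes the taper, worsens, and goes straight to bevacizumab or resection. The endpoint concerned is secondary, descriptive and without a threshold. This stands, and it is why the impact is judged small.

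A second reply is that rules on concomitant treatment and on carrying failures forward may be in the full protocol, which is not shown. That is fair for the carry-forward question. It does not answer the main point, because the article states its failure list as complete. Consensus review does not help either: it is for discrepant or equivocal findings, and a rescued patient with a clearly stable scan is neither.

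A third reply concerns the remedy. It carries the new failures forward while the article is silent on this for dexamethasone, and it would also cover minor agents such as pentoxifylline. Both observations are correct, but neither makes the remedy unsound. Scoring every treatment given for radionecrosis as non-response matches the comparators as the article describes them.

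**Conclusion.** The concern holds: the response rule is wrong as written, with small impact. A patient rescued by bevacizumab or resection without further dexamethasone can be credited to CHL, chiefly at 3 months. Each such patient adds 2.0 points (A) or 2.1 points (B). Three would add about 6 points, a little under half the sampling half-width.

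No expected bias is claimed, since the article gives no rescue rate. No formal decision changes at 3 months because no threshold exists there, and the 1-month primary endpoint is barely touched.

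For stratum B, only the rescue component is shown to be looser than the benchmark. The net direction over the whole endpoint is not established, because counting any increase on imaging as progression may be stricter than the benchmark.

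**What to change.** Add one sentence to section 2.5: starting bevacizumab, undergoing resection, or receiving any other treatment given for radionecrosis before an assessment counts as non-response at that and all later assessments. Patients with unequivocal tumour progression remain excluded, as the section already provides. It would help to say in the same place whether a month-1 failure on the existing three criteria also carries forward to month 3.

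The cost is low. These treatments are in the clinical record, and the change affects how a patient is counted, not the care given. Sample sizes and cut-offs stay as they are. The observed response rate may be slightly lower.

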**FIGURE 2 cam470657-fig-0002:**
[figure not shown]
Schematic representation of the conduct of the study.

### Sample Size Calculation

2.6

The proposed phase II prospective study will be split into two strata: Stratum A (symptomatic RN) and Stratum B (asymptomatic RN). Simon's two‐stage design (minimax) was used to calculate the sample size for each stratum, which is presented in Table 2.

**TABLE 2 cam470657-tbl-0002:** Sample size of the study with power estimates.

Stratum	Standard response rates	Expected response rates	Type 1 error	Power	No. of accrual 1st stage	No. of responses expected at 1st stage	Evaluation sample size at 1st stage (accounting for attrition 20%)	Total number of accrual needed for final analysis	Total no. of response expected for final analysis	Total sample size (considering attrition 20%)
Stratum A (Symptomatic)	50%	65%	0.0977	0.8022	22	10	27	50	29	60
Stratum B (Asymptomatic)	30%	45%	0.0963	0.8027	23	6	28	48	18	58

### Stratum A

2.7

The response rate at 1 month with a combination of steroids and CHL in this study is expected to be 65% as compared to the standard 50% response with the use of dexamethasone alone (based on institutional experience and available literature) [7, 8, 9, 19]. For the study with a α of 0.1 and power of 80%, 50 patients will be needed to achieve the desired output. In the first stage, 22 patients will be needed for assessment and continue to stage 2 if > 10 responses are seen. Stage 2 of the study will be considered successful if > 29 responses are achieved using the pre‐specified response assessment criteria. Further considering an attrition rate of 10% from lack of follow‐up and another 10% for disease progression, an estimated 60 patients will be accrued in stratum A with the purpose of achieving 50 patients with endpoints available for analysis.

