### Stratum B

2.8

This stratum includes patients without neurological worsening during the concerned imaging diagnosis of RN (asymptomatic RN). Based on the available literature and institutional experience, in this group, approximately 30% of patients continue to be neurologically/radiologically stable or show regression of imaging findings without the need for further interventions (including corticosteroids) in the short term [19, 20, 21]. In the proposed study with the use of CHL, 45% of patients are assumed to remain clinically and neurologically stable. With a α of 0.1 and a power of 80%, 48 patients will be needed to achieve the desired outcome. In the first stage, 23 patients will be needed for assessment and will continue to stage 2 if > 6 responses are seen. The phase 2 study will be considered successful if > 18 responses are achieved using the pre‐specified response assessment criteria. Further considering an attrition rate of 10% from lack of follow‐up and another 10% for disease progression, an estimated 58 patients will be accrued in stratum B with the purpose of achieving 48 patients with endpoints available for analysis.

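### The 20% attrition allowance multiplies the evaluable number by 1.2 instead of dividing by 0.8, so 60 and 58 accrued patients fall short of the 50 and 48 on which the 80% power rests

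*Protocol article*

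**What the plan says.** Section 2.6 states that a Simon two-stage minimax design "was used to calculate the sample size for each stratum". Table 2 and sections 2.7 and 2.8 then give:

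| | Stratum A | Stratum B |
|---|---|---|
| Null and target response rate | 50%, 65% | 30%, 45% |
| Stage 1 evaluable; continue if | 22; more than 10 responses | 23; more than 6 responses |
| Final evaluable; success if | 50; more than 29 responses | 48; more than 18 responses |
| Type I error, power | 0.0977, 0.8022 | 0.0963, 0.8027 |
| Accrual at stage 1, in total | 27, 60 | 28, 58 |

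The total-accrual column of Table 2 is headed "Total sample size (considering attrition 20"%). The text splits this into 10% for loss to follow-up and 10% for progression. It states what accrual is for: in A, "another 10% for disease progression, an estimated 60 patients will be accrued in stratum A with the purpose of achieving 50 patients"; in B, "an estimated 58 patients will be accrued in stratum B with the purpose of achieving 48 patients with endpoints available for analysis".

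Section 2.5 removes patients with unequivocal disease progression from the response assessment. The Discussion (section 3) says the same of recurrence documented within 3 months. The Abstract gives the total sample size as 118 (60 and 58).

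**The concern.** To have n evaluable patients left after losing a fraction d of those accrued, one must accrue n / (1 − d). Accruing n × (1 + d) gives too few. All four accrual figures in Table 2 follow the second form.

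The gap is a few patients, but a minimax design sits just above its power target, and success is set as a number of responses, not a proportion. Each evaluable patient lost lowers the chance of reaching that number, while the number itself stays the same. The go/no-go decision in each stratum would then be made with less power than the protocol claims. In the other direction, if more than 50 or 48 patients were evaluable and all were counted, the same fixed numbers would be easier to reach under the null and the type I error would pass 0.10.

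**Working it through.** **Inputs.** Response rates, stage sizes and cut-offs are those in the table above (Table 2, sections 2.7 and 2.8). Attrition is 10% + 10% = 20%. Both kinds of loss leave the denominator: progression under section 2.5, and loss to follow-up because sections 2.7 and 2.8 count only patients with an available endpoint.

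**Step 1: reproduce the design.** The probability of declaring success at true response rate p is

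P(success) = Σ over x > r1 of Bin(x; n1, p) × P[Bin(n − n1, p) ≥ r + 1 − x].

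- A (n1 = 22, r1 = 10, n = 50, r = 29): 0.0977 at p = 0.50 and 0.8022 at p = 0.65.
- B (n1 = 23, r1 = 6, n = 48, r = 18): 0.0963 at p = 0.30 and 0.8027 at p = 0.45.

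Both agree with Table 2, and a search confirms that both are the minimax designs. The error lies only in the attrition step.

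**Step 2: find where the accrual figures come from.**

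| Evaluable needed | × 1.2 | Stated | ÷ 0.8 |
|---|---|---|---|
| 22 (A, stage 1) | 26.4 | 27 | 27.5 → 28 |
| 23 (B, stage 1) | 27.6 | 28 | 28.75 → 29 |
| 50 (A, total) | 60.0 | 60 | 62.5 → 63 |
| 48 (B, total) | 57.6 | 58 | 60.0 → 60 |

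Every stated figure is n × 1.2 rounded up.

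**Step 3: what the stated accrual yields.**

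- At 20% attrition: 60 × 0.8 = 48.0 and 58 × 0.8 = 46.4.
- If the two 10% losses act in sequence (0.9 × 0.9 = 0.81): 60 × 0.81 = 48.6 and 58 × 0.81 = 47.0. This also falls short of 50 and 48.
- Attrition actually covered: 1 − 50/60 = 16.7% and 1 − 48/58 = 17.2%.

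**Step 4: error rates with the cut-offs as written.** This is the Step 1 formula with n replaced by the number attained.

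| Stratum, cut-off | Evaluable | Type I error | Power |
|---|---|---|---|
| A, > 29 | 50 | 0.0977 | 0.802 |
| | 49 | 0.0743 | 0.753 |
| | 48 | 0.0548 | 0.695 |
| B, > 18 | 48 | 0.0963 | 0.803 |
| | 47 | 0.0806 | 0.771 |
| | 46 | 0.0665 | 0.734 |

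**Step 5: random retention (secondary).** Suppose each patient is retained independently with probability 0.8. Then P[Bin(60, 0.8) ≥ 50] = 0.323 and P[Bin(58, 0.8) ≥ 48] = 0.370. Averaging the Step 4 power over that distribution, with all evaluable patients counted, gives about 66% in A and 73% in B.

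**Step 6: better retention (secondary).** If all evaluable patients are counted against the fixed cut-offs, the type I error in A is 0.155 at 52 evaluable and 0.26 at 55. In B it is 0.132 at 50.

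**Step 7: re-deriving the cut-off at the expected number.**

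- A at 48: > 28 gives type I error 0.094 and power 0.785.
- B at 46: > 17 gives type I error 0.1135, above 0.10, so > 18 must stay and power remains 0.734.

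**The case against.** The strongest reply is that the loss of power is conditional. The protocol calls 60 and 58 estimates and says they serve to obtain 50 and 48 patients with endpoints. If accrual simply ran until those numbers were evaluable, the design would be intact. That is true, but no passage says accrual continues in that way, and the Abstract states 118 as the total without qualification.

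Second, the shortfall is small: 3 and 2 patients, or 2 and 2 under sequential losses (62 and 60 needed), set against attrition rates that are round assumptions. The stage 1 discrepancy is a fraction of a patient (27 × 0.8 = 21.6 against 22; 28 × 0.8 = 22.4 against 23). It has little practical effect if stage 1 is read once 22 and 23 patients are assessable. This stands for stage 1. At the final analysis, the small gap still costs about 11 and 7 points of power.

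Third, part of the random-retention result is ordinary variation. Under the same model, accruing 63 and 60 reaches 50 and 48 only 62% and 58% of the time, with average power about 78% in both strata. This stands: the fair comparison is 66% with 78% in A and 73% with 78% in B.

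Fourth, the inflated type I error needs retention well above plan (55 of 60 is 8.3% attrition) and all evaluable patients counted. At the planned attrition, the average type I error is about 0.071 in A and 0.079 in B, so the slip makes the test conservative. This also stands, and the 0.26 is only an illustration of what fixed counts permit.

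Finally, adapting the cut-off is often left to the analysis plan. The finding does not depend on its absence, because the accrual figures contradict the protocol's own attrition assumption. Nor would re-deriving the cut-off restore B.

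**Conclusion.** The concern holds. The two-stage design and its error rates are right at 50 and 48 evaluable patients, but the accrual totals do not deliver those numbers at the attrition the protocol assumes. Expected evaluable numbers are 48 and about 46. With the stated cut-offs, power is 69.5% in A and 73.4% in B, against the 80% claimed.

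This rests on three conditions: accrual stops at 60 and 58, 20% are lost from the response analysis, and the cut-offs are applied as written. The first two are what the protocol plans, and it states no other cut-offs. Re-deriving the cut-off would bring A to 78.5% and leave B at 73.4%. The random-retention and type I error figures are secondary and are not needed for the conclusion.

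**What to change.** Correct Table 2 and sections 2.7 and 2.8 in one of these ways, and carry any change in the totals into the Abstract:

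1. Keep 60 and 58, and state that they allow for 16.7% and 17.2% attrition.
2. Keep 60 and 58 with 20% attrition, and state expected evaluable numbers of 48 and 46 with power of about 70% and 73% under the present cut-offs.
3. Accrue 63 and 60 (123 in total instead of 118), and change the stage 1 figures to 28 and 29.

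Whichever is chosen, add a sentence that the final cut-off is recomputed for the number of evaluable patients attained, by a rule fixed in advance that keeps the one-sided type I error at or below 0.10. Worked examples: A at 48, more than 28 responses (type I error 0.094, power 78.5%); B at 46, more than 18 (0.0665, 73.4%). If the intention is to accrue until 50 and 48 patients are evaluable, say so explicitly.

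Options 1 and 2 cost only wording and a restated figure. Option 3 costs five more patients.
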